### 520 **5.4 Endpoint Ascertainment**

521 At each annual visit and 6 month telephone contact, the participant will be questioned as to the  
522 occurrence of any of the study endpoints over the previous 6 months. Notification of a potential  
523 study endpoint will trigger the collection of information for endpoint confirmation and adjudication  
524 by the EAC. All such events will be recorded in source documents and in the appropriate  
525 section of the Case Report Form (CRF). Confirmation of endpoints will be ascertained by  
526 collecting and forwarding information from the following sources within 90 days of learning the  
527 event:

- 528 • Details from medical records from the usual treating physician or practice-held medical  
529 record.

- Medical records obtained by letter/fax/email contact with other treating specialist physicians or secondary/tertiary medical care centers.
- CRFs containing standardized questionnaires for the assessment of cognitive function, physical function and quality of life.
- In Australia, hospital records/discharge summaries, pathology reports, Medicare and Pharmaceutical Benefits Scheme (PBS) records.
- Death Certification: In both Australia and the U.S., the respective National Death Index will be routinely sourced for notification of death not identified through the above processes.
- For dementia endpoint ascertainment, the Dementia Adjudication Panel will be responsible for providing the assessment according to DSM-IV criteria. An individual's 3MS score below 78, or fall over time by more than 10 points adjusted for age and level of education, will trigger additional and uniformly applied cognitive and functional testing by research staff and the collection of ancillary data (laboratory tests and a CT or MRI) for endpoint ascertainment.
- For significant disability as a primary endpoint, the loss of one of the Katz Activities of Daily Living will be defined as self or proxy report of having 'a lot of difficulty with' or 'unable to perform' one or more ADLs at the annual follow-up contact. For all deaths where disability data is missing in the year preceding death, we will conduct a proxy interview to determine whether there was disability in the year prior to death and its approximate onset. We will also conduct a follow-up phone call to determine the persistence of the reported disability by repeating the same interview items.

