#### **7.1.1 Lifestyle Profile and Screening visit (Visit 1)**

Measurements and data will be collected by the research staff after the participant has provided informed consent to participate in the study. Each study participant will be assigned a unique identification number, which will be used throughout the study. The information to be collected at this visit (and thereafter at some or all Annual Visits\* - see Table 4) includes:

- a) Basic demographic and lifestyle factors including living situation\*, ethnicity and language, personal medical history\*, smoking history\*, alcohol use\*, medication history\* and level of education.
- b) Family history of acute MI, stroke, renal disease, colorectal and other cancers, or dementia – identified by the participant and from medical case notes.

- c) Blood pressure and heart rate\*: measured in the seated position following 5 minutes of rest using an oscillometric device. The average of three measurements taken 1 minute apart will be recorded.
- d) Cognitive function\* and depression: assessed using the Modified Mini-Mental State Examination (3MS) score  and the Center for Epidemiologic Studies – Depression 10 (CES-D)  questionnaires. The 3MS will be implemented as part of the screening of participants (where the score will be used to determine eligibility for the study) and will be administered again at years 1, 3, 5 and 7. The CES-D is a self-administered questionnaire used to screen for depression. It will be used in association with the 3MS, as depression is a confounder for cognitive function ascertainment, and also to ascertain new onset depression.
- e) Physical disability\*: assessed by the participant's self-reported ability to perform the 6 Katz Activities of Daily Living (ADLs), which form a component of the Lifestyle Interventions and Independence for Elders (LIFE) Disability questionnaire.
- f) Referral to a local Pathology Provider (in Australia) or direct collection of a fasting blood sample\* (~12 ml, for the measurement of total cholesterol, LDL-C, HDL-C, triglycerides, glucose, creatinine and hemoglobin) and urine spot test (minimum of 20 ml, to measure the albumin : creatinine ratio and detect the presence of microalbuminuria). Where available, a point-of-care instrument will allow prior screening for low hemoglobin levels.

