### **1.2 Incidence of all-cause dementia**

The trigger for a dementia assessment (assessment process is illustrated in Figure 1, Appendix 1) is a 3MS test score of  $\leq 77$ , or a reliable minimum change score of 10 points or more from baseline on the last test will trigger referral for dementia assessment with the cut-off being based on a regression model developed from the referenced community-based studies. This is necessary because as a predictor of dementia the change in an individual's 3MS is not linear across the range of scores (i.e. a change from 100 to 90 is not equal to a change from 90 to 80 or 80 to 70). Based on WHIMS data participants who score below education-specific cut points of  $<88$  ( $>8$  yrs education) and  $<80$  ( $<8$  yrs education) provide positive prediction probability of  $>0.90$  for dementia. Figures from the Edmonton community study of Bland and Newman, however, suggest a positive predictive value of about 0.33 for scores below 78. A clinical diagnosis of dementia noted in the medical records of any participant not already referred for dementia assessment will also trigger the same dementia assessment.

The diagnosis of incident dementia in ASPREE will be made on the basis of Diagnostic and Statistical Manual for Mental Disorders, American Psychiatric Association (DSM-IV) criteria, based on a standardized further assessment at least 6 weeks after the trigger event (tick-a-box DSM-IV assessment form). Diagnostic features include: memory impairment and at least one of the following: aphasia, apraxia, agnosia, disturbances in executive functioning. In addition, the cognitive impairments must be severe enough to cause impairment in social and occupational functioning. Importantly, the decline must represent a decline from a previously higher level of functioning. Finally, the diagnosis of dementia should NOT be made if the cognitive deficits occur exclusively during the course of a delirium. Classification of vascular dementia *versus* Alzheimer's disease or mixed dementia will not be requested, due to the lack of validated, clearly defined diagnostic criteria for vascular dementia. This triggered assessment will purposively utilize a different set of cognitive measures from those used in the routine visits to ascertain whether the cognitive aspects of the DSM-IV diagnosis of dementia are met:

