### **2.5 Mild cognitive impairment**

To assess the presence of Mild cognitive impairment (MCI) the routine visit battery of cognitive function tests (3MS, SDMT, Hopkins, COWAT) will be utilized. Figure 2, Appendix 1 illustrates the steps in assessment for MCI. Participants who have normal 3MS scores but whose Hopkins delayed recall and/or SDMT and/or COWAT test scores fall by more than 1 SD from their own baseline value will be provisionally categorized as having MCI. Normative data for the Hopkins will be obtained from the Hopkins VLT-R Manual, for the SDMT from the SDMT Manual (Western Psychological Services, 1982) followed by conversion from scaled scores, and for the COWAT from Kozora and Cullum^136. The advantages of using within-subject decline rather than a pre-specified cut-off of 1.5 SD below age-adjusted mean are that i) about 7% of the population function below 1.5 SD anyway, leading to a reduction in specificity, ii) decline is more indicative of likely (further) progression to dementia than a single cross-sectional low score, and iii) decline-based criteria can detect individuals with a progressive course before they fall below a defined cut-off of -1.5 SD (e.g.). For sub-classification of MCI, a decline in Hopkins delayed recall would be indicative of MCI-a (amnesic), a decline in either or both of the other tests indicates MCI-non-a (non-amnesic) and a decline in Hopkins delayed recall plus either of the

other tests indicates MCI-mixed.

In addition, those individuals who are triggered by a drop in 3MS score of  $> 10$  (adjusted for education level attained) or a score of  $< 78$  to undergo dementia assessment (see section 1.2), but who are not subsequently classified as having dementia based on DSM-IV criteria, will be provisionally categorized as having MCI. Even without a diagnosis of dementia, a decrease in 3MS score of  $\geq 10$  points is a measure of clinically significant cognitive decline. Assignment to MCI subcategories in these participants will be made by the endpoint adjudication committee on the basis of results from the routine cognitive exam and the triggered assessment. If no individual tests (other than the 3MS) have declined sufficiently to enable sub-categorization, the default category will be MCI-mixed.

[figure not shown]

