Appendix 1. Figure 2.  
Flowchart for Mild Cognitive Impairment assessment to reach a secondary endpoint.  
MCI-a (amnesic); MCI-non-a (non-amnesic)

In all cases, the provisional diagnosis of MCI will require confirmation of the decline (i.e. relevant result(s) still  $> 1$  SD below baseline, or 3MS still  $> 10$  (adjusted) points below baseline, or still  $< 78$ ) at reassessment at 12 months. For those showing a decline indicative of MCI only at the last assessment, reassessment confirming the decline will be required 3 months later. (The 1 year timing allows reassessment to occur at the time of a scheduled routine visit, reducing assessment costs. The 3 month interval for those declining only at the final assessment avoids delaying analysis and publication unnecessarily.)

MCI, as traditionally defined by a deficit of  $-1.5$  SD in a cognitive domain or domains in the presence of preserved general cognition (3MS  $> 77$ ), is not a study entry exclusion criterion. While those subjects ultimately destined to decline to dementia will be picked up at subsequent

2167 assessments on the decline criteria used in ASPREE for MCI, a planned sub-group analysis will  
2168 also be performed on the MCI category and sub-categories, after exclusion of any falling below -  
2169 1.5 SD on the relevant measure on entry.

2170 We wish to emphasize that MCI is a secondary endpoint and that one of ASPREE's strengths is  
2171 that its test battery will allow several alternatives to identifying and defining MCI that may be  
2172 useful for future large trials in this population.

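### Read literally, a dementia diagnosis in the medical records prompts no standardized assessment in anyone referred before; other routes remain, so this is a cheap wording fix

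*Protocol*

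**What the plan says.** Appendix 1, section 1.2, gives two ways into the dementia assessment.

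- **3MS.** A score of 77 or lower, "or a reliable minimum change score of 10 points or more from baseline on the last test will trigger referral for dementia assessment". Nothing limits this trigger to a first occurrence.
- **Medical records.** A "clinical diagnosis of dementia noted in the medical records of any participant not already referred for dementia assessment will also trigger" the same assessment. This route carries a condition about earlier referral.

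The same section says that community data "suggest a positive predictive value of about 0.33 for scores below 78", so many referrals on a low score are expected to end without a dementia diagnosis. Appendix 1, section 2.5, keeps these participants in the trial: those who were triggered "but who are not subsequently classified as having dementia based on DSM-IV criteria, will be provisionally categorized as having MCI". That classification must be confirmed "at reassessment at 12 months", or 3 months later when the decline appears only at the last assessment. A 3MS that is still low is one of the confirming results.

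Section 7.1.1 says that the 3MS "will be administered again at years 1, 3, 5 and 7", and the notes to Table 4 give every final visit the year-7 measures. Under section 5.4, notification of a potential "study endpoint will trigger the collection of information for endpoint confirmation and adjudication". In section 5.4's bullet on dementia, however, the uniform cognitive and functional testing starts only from 3MS results.

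**The concern.** The condition on the record-based trigger turns on whether a participant was ever referred. What matters for the endpoint is whether the participant has already been found to have dementia. Two participants with the same new diagnosis in their records are therefore handled differently: one never referred is assessed, while one assessed two years ago and found not demented is not, at least by this route.

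The second participant belongs to a group that the protocol itself regards as at raised risk. Section 2.5 calls a 3MS fall of 10 points or more clinically significant, and treats decline as a sign of likely progression to dementia.

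Dementia is a component of the primary endpoint and a secondary endpoint. An assessment that was never done cannot be recovered in the analysis.

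**Working it through.** **1. What happens after a negative assessment.** Take a participant referred on the 3MS, assessed, and classed as provisional MCI, whose records later show a clinical diagnosis of dementia.

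| Route | Open to this participant? | Limit |
|---|---|---|
| Record trigger (App. 1, 1.2) | No, read literally | Earlier referral closes it |
| 3MS trigger (App. 1, 1.2) | Yes, at years 1, 3, 5, 7 and the final visit | Up to two years between scheduled tests; none after the last |
| MCI recheck (App. 1, 2.5) | Yes, at 12 or 3 months | Written to confirm MCI; a new dementia referral is not stated |
| General notification (5.4, 5.5) | Yes; records reach adjudicators, who may ask for more | Does not itself start the uniform tests on which 1.2 has adjudicators decide |

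One route closes and three stay open. The gap is a diagnosis that falls between 3MS tests or after the last one.

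**2. The plan's own power figures.** With 1:1 allocation and two-sided alpha 0.05, power = Φ(|ln HR| × √events / 2 − 1.96).

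- Primary endpoint (Appendix 2): 311 + 3374 = 3685 events at HR 0.90 give 89.2%; the protocol states 89%.
- Dementia rate, from Appendix 2's original age mix and main incidence rates: 0.50×6 + 0.30×11 + 0.15×20 + 0.05×37 = 11.15 per 1000 person-years.
- Dementia events: 19,000 × 4.25 years × 11.15/1000 ≈ 900, using the placebo rate in both arms. At HR 0.807 this gives 89.6%; the protocol states 90%.

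**3. Illustration of the loss.** Three inputs are not in the documents and are assumptions:

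- every case enters through the 3MS at the 0.33 predictive value, so negatives = (0.67/0.33) × F = 2.03F, where F is the number found at first assessment;
- 5-15% of the negatives convert per year over a mean of 2 remaining years, a fraction q = 1 − exp(−2c) = 0.095 to 0.259;
- 20-40% of converters have no later 3MS, and all of these are lost.

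First-assessment cases and later converters together must make up the 900, so F × (1 + 2.03q) = 900.

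| Conversion per year | F | Converters | Lost at 20% | Lost at 40% |
|---|---|---|---|---|
| 5% | 754 | 146 | 29 | 58 |
| 15% | 590 | 310 | 62 | 124 |

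The range is 29 to 124 events, or 3% to 14% of 900. Dementia power is 88.6% with 871 events and 84.8% with 776.

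**4. Effect on the composite.** Appendix 2 gives an ADL rate of 0.45×19.6 + 0.55×26.5 = 23.40. Its Australian mortality rates, weighted by age and sex and halved as assumed there, give 18.51. Dementia's share of the summed rates is 11.15/(11.15 + 23.40 + 18.51) = 21%, or about 774 of 3685 first events. Losing 3-14% of these (about 25-107 events) leaves power at 89.0-88.3%. This ignores lost cases that still enter the composite through later death or disability.

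**The case against.** The strongest reply is that the condition is there only to avoid duplicate referrals. It follows directly on the 3MS rule and can be read as saying that someone already sent for assessment on a score need not be sent again. The text does not say that a participant ever assessed is excluded for good, and the flowchart that illustrates the process is not available in the copy reviewed. This may well be the intent. It does not settle the point, because the wording draws no line between a pending referral and one that ended negative, and no text shown restores the trigger.

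The second reply stands in large part. A reader might infer that the next scheduled 3MS is the only dementia-specific route left, and that detection is least sensitive in the group most likely to convert. The documents do not support that. These participants have an additional recheck at 12 or 3 months that can include the 3MS, the 3MS trigger can fire again, the final visit includes the 3MS, and section 5.5 lets adjudicators request further information.

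A reader might also infer a larger loss. Treating all 900 dementias as found at first assessment gives about 1,800 negatives, up to about 190 lost events (21%) and power of about 82%. That counts the same cases twice, because the later converters are themselves among the 900.

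Finally, the 0.33 applies only to scores below 78, not to the 10-point fall or to record-based referrals. The 20-40% without a later 3MS has no source, and is hard to reach among participants who still attend, since another 3MS is scheduled for them.

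**Conclusion.** The gap is real but narrow. As worded, Appendix 1, section 1.2, leaves a new clinical diagnosis in a previously negative participant without a fresh standardized assessment by the record route. Some dementia events may then be dated late or missed.

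The size cannot be derived from the documents. The 3-14% loss, with dementia power of about 89-85%, is an upper-end illustration that depends on the three assumptions in the working. Composite power stays near the stated 89%. The rule is the same in both arms, so no directional bias is shown, and none of the protocol's stated figures is wrong. This is a cheap improvement.

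**What to change.** In Appendix 1, section 1.2, replace the condition that the participant has not already been referred with: *not already adjudicated as having the dementia endpoint and without an assessment in progress*. Add one sentence: a new clinical diagnosis of dementia recorded after an earlier negative assessment triggers the same assessment and a fresh adjudication.

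This still prevents duplicate referrals. The cost is one phrase, one sentence, and a small number of repeat assessments with the existing battery.

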Appendix 1. Figure 1.  
Flowchart for dementia assessment to reach a primary endpoint.

### 1.3 Loss of physical ability for activities of daily living

We will define activities of daily living disability on the basis of inability or severe difficulty with performance of one or more of the six Katz ADLs. The instrument will be administered by interview at baseline and every six months. This outcome definition of disability has a long tradition in the geriatric literature, and is salient to both the physician community and the public. The rate of ADL disability increases with age, but it not often reported for age, sex and race strata. In a sub-group of the Cardiovascular Health Study participants matched for age and inclusion criteria ([name], personal communication, 8/2008) the rate of ADL disability was about 2% per year, higher in women than men.

The Katz ADLs include walking, bathing, dressing, transferring from a bed or chair, using the toilet, and eating. For ASPREE, we will use questions adapted from Katz for the Established Populations for the Epidemiologic Study of the Elderly (EPESE). The original Katz items were classified by a health professional based on observation. These were adapted for self-report in the EPESE and are used in clinical trials and observational studies. These ADL items can be used alone but have also often been combined with items addressing IADLs and higher level mobility such as in the EPESE, CHS, LIFE and other studies. The questionnaire queries perceived difficulty in activities of daily living during the previous month. The following response options will be used, as were adapted from EPESE for the CHS study: (1) no difficulty, (2) a little difficulty, (3) some difficulty, (4) a lot of difficulty, or (5) unable to perform^118. Use of these same items allows comparability of assessments for rates comparisons for many NIA-supported studies over many years.

1968 We will also ask about “need for assistance” but will not define the outcome as dependency  
 1969 (‘need for assistance’) because this aspect of disability has been shown to be determined in part  
 1970 by available assistance and socioeconomic status, while reported difficulty is more directly  
 1971 related to actual performance. Self-report of ‘inability’ is rare in healthier older adults, such as  
 1972 would be selected for the ASPREE study, while severe difficulty is more commonly endorsed.  
 1973 Rates of this combined degree of difficulty were about 2% per year in the CHS study for a sub-  
 1974 cohort matched for age and other inclusion criteria to the ASPREE sub-cohort. Rates of ADL  
 1975 inability alone in this simulation were <0.5% per year, thus too infrequent an outcome for clinical  
 1976 trial. Therefore, for the primary endpoint ascertainment, a loss of function will be deemed to be a  
 1977 report of ‘a lot of difficulty’ or ‘unable to perform’ the ADL by self-report. For participants who are  
 1978 unable to answer due to illness, a proxy will be asked to answer these same items on behalf of  
 1979 the participant. For participants who miss a 6 month interview before death, a proxy decedent  
 1980 interview will be conducted to address the time frame of the onset of disability. This method has  
 1981 allowed classification of disability before death in the Health ABC study. If all information is  
 1982 missing, the date of death will be used in the primary outcome as the first event and for disability  
 1983 analyses follow-up will be censored at last contact.

1984 We will evaluate persistence of ADL disability as a primary endpoint. This will be done by  
 1985 reassessing level of disability using the same items at a subsequent 6 month telephone call or  
 1986 annual visit after the initial report. If the subsequent contact is missing, a proxy will be contacted  
 1987 for this information. If death precedes this follow-up contact, the death will be counted as the  
 1988 endpoint. If the subsequent contact is missed, but followed by death, persistent disability will be  
 1989 presumed. This method has worked well in determining persistent disability in the Health ABC  
 1990 study.

## 1991 **2. Secondary Endpoints:**

- 1992 1. All-cause mortality
- 1993 2. Fatal and non-fatal cardiovascular events including a) coronary heart disease
- 1994 death, b) non-fatal myocardial infarction, c) fatal and non-fatal stroke and d)
- 1995 hospitalization for heart failure.
- 1996 3. Fatal and non-fatal cancer, excluding non-melanoma skin cancer
- 1997 4. Dementia
- 1998 5. Mild cognitive impairment (MCI)
- 1999 6. Physical ADL disability
- 2000 7. Depression
- 2001 8. Major hemorrhagic events

